## Data collection and procedures

### Standardization

To the most possible standardized and similar inclusion process all GPs participating in the study will be educated in the inclusion procedures by the principal investigator and one senior investigator whom will visit all clinics before the initiation of the study.

### Day 0/inclusion

When consulting a patient examined and considered a suitable participant according to the inclusion and exclusion criteria, the GP will give the patient the opportunity to participate in the study. If the patient is still willing to participate, the patient will sign a form of consent with the GP, be scored by the GP on initial symptom load, and give a urine sample which will be sent with the questionnaire to the central laboratory and optionally examined with dipstick

### Follow-up

The investigators at the central laboratory will be calling or sending text messages (patient’s decision) to the included patients to follow-up on the questionnaires and control urine-samples, as well as answering any questions the patients might have. The phone calls or text-messages are app. made on day 3–5, day 9–11 and day 28–30, respectively. However, not at any time will we try to increase the adherence to the treatment, since the study ought to be mirroring a realistic patient situation.

### Criteria for termination from the study

If a patient during the study would develop signs of upper UTI (i.e. pyelonephritis), treatment failure, serious adverse effects or allergic reactions to the medicine, or decision of withdrawal, she will have to terminate from the study and possibly get a new evaluation by a physician.

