### Second medical consultation

Patients will be told at recruitment to visit the GP again if she develops worsening of symptoms or not experiencing any symptom relief during the study period. In that case the GP is able to choose a new treatment strategy for the patient and will have the potential microbiological diagnostic answers (i.e. from pre-treatment urine sample) to take in consideration in this approach.

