### Secondary endpoints

Clinical signs and symptoms in uncomplicated LUTIs in women.Frequency and timing of relapse of symptoms and/or bacteriuria.Bacteriological findings (i.e. ESBL producing bacteria).Complications (i.e. urosepsis and/or pyelonephritis) within 28 days.

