### Procedures to evaluate endpoints

By comparing the questionnaires we can evaluate the clinical endpoints. By examining the urine samples we can evaluate the bacteriological endpoints. By asking for a questionnaire on day 28 we can evaluate any relapse/reinfection, hospitalization or secondary consultation, and afterwards look in the collaborating department of clinical microbiology’s databases for urosepsis or pyelonephritis.

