### Power analyze

We hypothesize that there is a 15% absolute differences in efficacy between the groups, measured in clinical efficacy. We believe there to be an even bigger difference in bacteriological efficacy. Assuming an efficacy of 90 and 75% for 5 days and 3 days therapy, respectively, using a double-sided test with *p* < 0.05, and a statistical power of 0.8, we will need 113 patients in each group for the NTT analysis. With an estimated fall-out rate of app. 30% between each arm; 161 patients per group will need to be included for the PP analysis, and 230 in each group for the ITT analysis. There is a possibility for an interim analysis after 300 included participants, since we cannot reject a possibility for a higher (i.e. 20%) absolute efficacy.

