### Adverse effects/risks

Pivmecillinam has been proven in RCTs to be safe and effective in the treatment of UTIs [6, 8, 20]. The risk off selecting and spreading off for mecillinam resistant bacteria is at very low risk [11], and mecillinam has a minor impact on the normal microflora [21]. Side effects are not more common than in any other penicillin, severe side effects are very rare, and the most common side effects are gastrointestinal complaints (i.e. nausea). Other common side-effects are rash and vulvovaginitis [6]. In the questionnaires the patients will be asked for possible adverse effects on day 1–7 and day 28. Any adverse reactions, serious adverse reactions or events during the study period will be reported according to GCP principles and in concordance with the Danish National Health and Medicine Authority.

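### The termination rule ends follow-up, and not only study tablets, for patients with upper UTI, treatment failure, serious adverse effects or allergy, so their later events are not systematically collected

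*Protocol article*

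**What the plan says.** The protocol article, Criteria for termination from the study, deals with a patient who develops signs of upper UTI, "treatment failure, serious adverse effects or allergic reactions to the medicine, or decision of withdrawal, she will have to terminate from the study". It adds that she may be re-evaluated by a physician. Four clinical events and withdrawal by choice stand in one list with one mandatory consequence.

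Other sections describe data collection up to about day 28:

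- Follow-up: "The phone calls or text-messages are app. made on day 3–5, day 9–11 and day 28–30". These contacts go to the included patients and serve to obtain questionnaires and control urine samples. No exception is made for patients who fail.
- Second medical consultation: patients are told to "visit the GP again if she develops worsening of symptoms or not experiencing any symptom relief during the study period".
- Procedures to evaluate endpoints: "By asking for a questionnaire on day 28 we can evaluate any relapse/reinfection, hospitalization or secondary consultation". A search of the microbiology department's databases is added, named only for urosepsis and pyelonephritis.
- Secondary endpoints: "Complications (i.e. urosepsis and/or pyelonephritis) within 28 days".
- Adverse effects/risks: "In the questionnaires the patients will be asked for possible adverse effects on day 1–7 and day 28". More generally, "Any adverse reactions, serious adverse reactions or events during the study period will be reported according to GCP principles".
- Definitions, under Power, sample size and analysis: the ITT set holds every included patient.

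**The concern.** A patient who stops study tablets because of failure or a reaction is normally still followed, since what happens to her next is part of the treatment's effect. The termination section gives her the same exit as a patient who withdraws. A site that follows it literally stops contacting her and does not collect the day-28 questionnaire.

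That questionnaire is the planned source for hospitalisations and second consultations, and the systematic source for adverse effects at day 28. The patients likely to have most to report there are those whose reporting ends early. Because failure is one of the triggers, and the trial expects more failures on 3 days than on 5, collection could also be less complete in one arm than in the other. An analysis plan can say how to handle missing data, but it cannot recover a questionnaire that was never collected.

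**Working it through.** The article gives no termination rate, so there is no figure of its own to reproduce on this point. The check is mainly a comparison of sections, followed by simple arithmetic on direction.

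**1. Does any section keep a terminated patient in follow-up?**
- Follow-up schedules contacts to day 28–30 for included patients but does not mention termination.
- The ITT definition keeps every included patient in the analysis but does not say that data are still collected after termination.
- Intervention provides for a second antibiotic after failure, meaning persisting or worsening symptoms, and mentions neither exit nor continued follow-up.

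These sections suggest that follow-up may have been meant to continue. None says so, and the termination section is mandatory.

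**2. Which sections does the rule sit badly with?**
- Follow-up: contacts run to day 28–30, while the rule ends participation earlier.
- Procedures to evaluate endpoints: consultations and admissions are to be read from a questionnaire that terminated patients would not return.
- The ITT definition: all included patients are analysed, some without later data.

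Second medical consultation, and Procedures in the Discussion, send patients with failure back to the GP. This agrees with the re-evaluation by a physician in the termination section, so there is no conflict there.

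**3. What is lost and what is kept?**

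| Item | Source in the article | After termination, as written |
|---|---|---|
| Urosepsis, pyelonephritis | Database look-up after the questionnaire | Partly protected |
| Consultation that reveals the failure | May be what prompts termination | May already be known |
| Further consultations, later hospitalisation | Day-28 questionnaire | Not systematically collected |
| Adverse effects at day 28 | Day-28 questionnaire | Not systematically collected; general safety reporting may capture some |

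**4. In which direction would the loss differ between arms?**

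Input, from Power analyze: "Assuming an efficacy of 90 and 75% for 5 days and 3 days therapy, respectively". Non-cure is 1 − 0.75 = 0.25 on 3 days and 1 − 0.90 = 0.10 on 5 days. Let s3 and s5 be the shares of uncured patients who are terminated in the 3-day and 5-day arms. Neither is given.

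Ratio of terminations for failure, 3-day to 5-day = (0.25 × s3) / (0.10 × s5) = 2.5 × s3/s5.

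- s3/s5 = 1 (assumption): 2.5
- s3/s5 = 0.5 (assumption): 1.25
- s3/s5 = 1.5 (assumption): 3.75
- The ratio falls to 1 only at s3/s5 = 1/2.5 = 0.4.

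This restates the plan's hypothesis and shows direction only. Non-cure means a symptom score of 2 or more, which is not the same as a failure that leads to termination: a patient who is improving but still scores 2 need not be terminated. Failures in the first three days, when both arms take the same drug, pull the ratio towards 1. Terminations for adverse effects or allergy are outside it. No counts are computed, because the rates are stated for the NTT set, which is drawn from patients with complete follow-up and so cannot be applied to everyone included.

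**The case against.** The strongest reply is that this is loose wording in a condensed article. The contact schedule and the ITT definition make no exception for failures, so the authors may have meant only that study treatment ends, and the full protocol may say so. That is plausible. But the article states a rule rather than leaving the matter open, and the rule names leaving the study, so it is more than missing detail.

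The second reply is that the loss falls on items of lesser rank. Second consultation and hospitalisation are not listed among the co-primary or secondary endpoints. Relapse requires an initial cure, so a patient who was never clinically cured is not a candidate for clinical relapse. This stands and limits the weight of the point. Consultations and admissions are nevertheless evaluations that the article plans explicitly.

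The third reply concerns adverse effects. General safety reporting covers the study period and may capture some later events, although it is unclear whether it extends to a terminated patient. After a switch of antibiotic, later adverse effects also reflect the new drug. Both points stand, so the clearer loss is in hospitalisation and further consultations.

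A reader might go further in three ways that the article does not support:

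- That the complications endpoint is lost. The database look-up remains for urosepsis and pyelonephritis.
- That the rule contradicts the instruction to return to the GP. The termination section itself foresees a new medical evaluation.
- That the cure comparison is diluted because terminated failures drop out of the PP and NTT sets. The article does not say that a terminated failure counts as a dropout, and it gives no share of failures terminated.

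**Conclusion.** The point holds as a badly fixed rule. Read as written, follow-up ends because of outcome for patients with upper UTI, treatment failure, serious adverse effects or allergic reactions. Later hospitalisations, further consultations and questionnaire-reported day-28 adverse effects are then not systematically collected for them, while the ITT set still counts them.

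If the plan's efficacy assumption is right, terminations for failure would probably be more frequent in the 3-day arm. That rests on the assumed 25% and 10% non-cure and on the arms not differing greatly in the share of uncured patients who are terminated. The ratio of 2.5 should not be read as the size of a loss or of a bias; neither the number terminated nor any bias can be derived from the article. The limits named above make this a correction worth making, not a threat to the trial's main comparison.

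**What to change.** Reword Criteria for termination from the study so that upper UTI, treatment failure, serious adverse effects and allergic reactions end study medication where applicable, but not follow-up. Treat withdrawal of consent separately, as the only one of the listed reasons that ends follow-up.

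State that, unless consent is withdrawn, the contacts already planned and the day-28 questionnaire are kept for every randomised patient, and that the database look-up for urosepsis and pyelonephritis covers all of them.

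The contacts, the questionnaire and the look-up already exist, and the sample size does not change. The downside is a few more completed contacts by existing staff.

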### Second medical consultation

Patients will be told at recruitment to visit the GP again if she develops worsening of symptoms or not experiencing any symptom relief during the study period. In that case the GP is able to choose a new treatment strategy for the patient and will have the potential microbiological diagnostic answers (i.e. from pre-treatment urine sample) to take in consideration in this approach.

## Outcome

### Primary endpoint

We have two co-primary endpoints:
**Co-primary endpoint no. 1** –clinical efficacy (i.e. which group will be clinically cured fastest and proportion of patients cured at day four).
**Co-primary endpoint no. 2** – bacteriological efficacy (i.e. proportion of patients bacteriologically cured at first control urine sample).

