## Data processing and statistical analysis

The source data is the GP’s and patient’s questionnaires and the diagnostics answers from the microbiological lab at the DCM. All source data will all be stored by the investigator and sponsor, in originals and scanned copies, at the DCM. The collected source data are transferred, logged and processed in the computers of the DCM. Analysis will be made in ITT, PP, and NTT form, respectively. All data will be analyzed coded, and only de-coded after the analysis is done and the analytic results are written in the relevant sections in the future article. The statistical software packages SAS (SAS Institute, Cary, NC) will be used for all analyses. Categorical data will be analyzed using a Fisher’s Exact test.

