### Outcomes

The primary outcome we want to focus on is the clinical effect, since that is of most importance to the patient. However, it is important to know that the bacteria disappear and not cause clinical relapses in the future; therefore, we included two follow-up urine sample at day-4 and day-28, respectively.

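### Two co-primary endpoints hold three measures, analysed in three sets with no decision rule or primary set, so the 5% error rate and the 80% power cannot both be assured

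*Protocol article*

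**What the plan says.** **Endpoints.** Under Primary endpoint the article says "We have two co-primary endpoints". The first is clinical efficacy, described as "which group will be clinically cured fastest and proportion of patients cured at day four". The second is bacteriological efficacy, the "proportion of patients bacteriologically cured at first control urine sample". That is three measures under two labels. The section does not say whether one, both or all must be significant.

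**Analysis sets.** Data processing and statistical analysis states: "Analysis will be made in ITT, PP, and NTT form, respectively". None of the three is named primary. The Definitions under Power, sample size and analysis draw NTT from PP, so NTT already excludes dropouts.

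**Error rate and power.** Power analyze gives one calculation, "using a double-sided test with *p* < 0.05" and power 0.8, for clinical efficacy of 90% (5 days) against 75% (3 days). The result is 113 per group for NTT, raised to 161 for PP and 230 for ITT. On the second endpoint it says only: "We believe there to be an even bigger difference in bacteriological efficacy".

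**Emphasis.** The Outcomes part of the Discussion says: "The primary outcome we want to focus on is the clinical effect". It sets no order of testing.

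**The concern.** The section on scientific and societal perspective ties a change of guidelines to significant superiority of the 5-day course, without saying on which endpoint or in which set. As written, that claim could rest on any of the three measures in any of the three sets. The choice could be made once it is known which comparisons reached significance. Keeping the treatment codes closed until the analysis is written up does not prevent this, because the significant results are visible without the arm labels.

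The rule also decides what the sample size means. Any-one-suffices needs a smaller alpha per test. Both-required needs more power per test. The 113 was computed for neither.

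**Working it through.** **1. Reproduce the plan's figure.** Inputs from Power analyze: 0.90 and 0.75, two-sided 0.05, power 0.8. Mean rate 0.825.

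- n = [1.960 × √(2 × 0.825 × 0.175) + 0.842 × √(0.90 × 0.10 + 0.75 × 0.25)]² / 0.15² = 99.5, so 100 per group.
- With continuity correction: (99.5/4) × [1 + √(1 + 4/(99.5 × 0.15))]² = 112.5, so **113**. This matches.
- Fall-out: 113/0.7 = 161.4 and 161/0.7 = 230.0. The 161 and 230 are divisions by 0.7, not power calculations for PP or ITT.
- Exact power of Fisher's test at 113 per group is 81.7%. The stated power holds for this one comparison.

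**2. If any one measure suffices, in one set.** Each test is taken at nominal 5%.

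- Three independent tests: 1 − 0.95³ = 14.3%.
- Correlation 0.5 between measures (assumed; simulation, 400,000 draws): 12.5%.
- Allowing for Fisher's conservatism: its actual size at 113 per group is 2.8% to 3.6% for common cure rates from 0.90 to 0.75. With 3.4% for the two binary measures and 5% for speed of cure, 1 − 0.95 × 0.966² = 11.3% if independent, and about 10% at correlation 0.5.

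**3. If any set may also be chosen.** The sets are nested, so their statistics are correlated at √(113/161) = 0.84, √(161/230) = 0.84 and √(113/230) = 0.70. Simulated nominal error:

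| Correlation between measures (assumed) | Any of three measures, any of three sets |
|---|---|
| 0 | 26.4% |
| 0.5 | 23.4% |
| 0.7 | 20.4% |

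One measure picked across the three sets gives about 10%. Nine independent tests would give 1 − 0.95⁹ = 37%, which is only an upper bound.

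**4. If both endpoints are required** (one clinical measure plus bacteriology). Error is at or below 5%. Joint power at 113 per group:

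- 80% each, independent: 0.8 × 0.8 = 0.64; at correlation 0.5, 0.69.
- The article expects a larger bacteriological difference but gives no figure. Assuming 90 v 70%, Fisher power is 96.1%, and 0.817 × 0.961 = 0.785.
- If both clinical measures are required as well, 0.817 × 0.817 × 0.961 = 0.64, taking speed of cure to have the same power as the day-four comparison (assumed).

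For 80% joint power with two equal, independent effects, each test needs √0.8 = 89.4% power. That is 144 per group with continuity correction, against 113.

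**The case against.** **Neither figure holds.** A reader might infer this, but it goes too far. An either rule inflates error while power rises. A both rule lowers power while error is held. Only a mixed rule, in which either part of the first endpoint plus the second suffices, touches both: error up to 9.75%, and power (1 − 0.2²) × 0.8 = 0.77.

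**Nine tests at 0.05.** The article does not say this. The threshold appears once, as a sample-size input. The 20–26% describes what the text leaves open, not a stated procedure.

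**Contradiction between sections.** The Discussion's preference for the clinical effect might be read as contradicting two equal endpoints. It is better read as emphasis, since the same paragraph goes on to justify the bacteriological endpoint.

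**Power claimed for PP and ITT.** The article attaches 0.8 to the 113 in NTT, so it does not clearly claim 80% power for the other sets.

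**Left to the analysis plan.** A decision rule and a primary set are often set there, and that document is not shown. This is the strongest objection, and the absence of wording alone would not be a finding. What remains is that the article itself fixes the co-primary structure, one undivided alpha, one power and the sample size. Under no reading that uses all three measures do these fit together without a further rule.

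**Size.** The power loss is modest if the bacteriological effect is as large as expected, and Fisher's conservatism trims the error inflation. Both points stand and are reflected in the ranges.

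**Conclusion.** The point holds in limited form. Until a decision rule and a primary set are fixed, the 5% error rate and the 80% power cannot both be assured.

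- Any one measure suffices: error about 12.5–14% nominal in one set, about 10–11% after allowing for Fisher's test, and about 20–26% if the set is also free.
- Both endpoints required: error held, joint power about 0.64 to 0.785.

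The ranges rest on assumed correlations between measures (0 to 0.5 in one set, 0 to 0.7 across sets), independence for the joint power, and an assumed 90 v 70% for bacteriological cure. The sponsor should act on this, but it does not invalidate the calculation of 113 for its single comparison.

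**What to change.** 1. **Primary endpoint:** keep one clinical measure, the proportion clinically cured, because the sample size is for a binary clinical comparison. Move speed of cure to the secondary endpoints. Test the clinical proportion at two-sided 0.05, then bacteriological cure at two-sided 0.05 only if the first is significant.
2. **Data processing and statistical analysis:** name one primary analysis set and label the other two supportive.
3. **Power analyze:** state that 0.8 applies only to the clinical comparison in NTT as the article defines it, with 113 per group having outcome data, and that 161 and 230 are fall-out inflations. If another set or a both rule is chosen, restate the power for it.

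Step 3 matters if the primary set is to be susceptible culture-positive patients drawn from everyone randomised. That is not the set behind the 113. It would hold about 161 per arm, and if the 30% without data count as failures (0.7 × 90% = 63.0% v 0.7 × 75% = 52.5%), Fisher power is about 43%.

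**Cost:** wording only, with no added patients under the fixed order. Bacteriological superiority cannot be claimed if the clinical test fails. A both rule could cost more: in the equal, independent case, 144/0.7/0.7 = 294 per group, or 588 in all, against the 500 kits planned.

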#### Intervention

All patients included will receive pivmecillinam therapy for 3 days or 5 days. The 3-day regimen group will receive blinded placebo tablets on day 4 and 5. If a secondary antibiotic treatment is required due to treatment failure (i.e. ongoing or worsening symptoms), a new antibiotic cure will be chosen in line with the results from the pre-treatment (inclusion day) urine culture. The GPs will be at any time welcome to call the Department of Clinical Microbiology (DCM) (i.e. central investigation site) for consultation in the matter.

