#### Questionnaires

The GP will receive an inclusion-questionnaire that he/she will fill out on day 0 (inclusion day). The questionnaires his will include age, positive inclusion criteria (i.e. LUTI symptom load), exclusion criteria, debut date of symptoms, and annual incidence of LUTI. All participants will be given a diary-questionnaire for day 0 to day 7*.* In which they daily will answer questions on LUTI symptoms, score them of severity on daily bases and report on which day they feel completely cured (i.e. back to habitual conditions). They will also be asked to register impairment in daily life activities and quality (i.e. work, physical activity, sleep, mental well-being) similar to the symptom score, previous UTI, travel, weight (i.e. >70 kg) possible adverse effects, adherence to the therapy, use of analgesics and other optional information. The patient will also receive a second follow-up questionnaire which need to be filled out once anytime around day-28 (i.e. possible symptoms or side effects since end of therapy, current status of questions asked in the symptom-diary). All questionnaires on symptoms are constructed according to the validated questionnaires for LUTI symptom score [16]. They will be submitted together with the urine samples. All of the patients’ questionnaires will be so patients can easily understand and answer the questions.

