### Definitions

Clinically cured is defined as cumulative symptom score of <2.Clinical relapse is defined as initial clinically cured followed by cumulative clinical score of ≥2 at day 28.Bacteriologically cured is defined as significant reduction (i.e. ≥ 10^2^ fold decrease in uropathogenic bacteria) or potentially full eradication of uropathogenic bacteria (i.e. sterile culture or asymptomatic contaminations of non-uropathogenic bacteria).Bacteriological relapse is defined as initially bacteriologically cured followed by significant growth at day-28, with the same bacteria. Growth of other uropathogenic bacteria is defined as reinfection.

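### The only clinical co-primary proportion is read at day four, as the arms begin to differ, while the sample size assumes 90% v 75% for complete courses with no time point

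*Protocol article*

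**What the plan says.** All references are to the protocol article.

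- *Primary endpoint*: the clinical co-primary has two parts, "which group will be clinically cured fastest and proportion of patients cured at day four". The bacteriological co-primary is the proportion cured at the first control urine.
- *Definitions* (under Outcome): "Clinically cured is defined as cumulative symptom score of <2".
- *Intervention*: "The 3-day regimen group will receive blinded placebo tablets on day 4 and 5". Until then both arms take the same active tablets.
- *Power analyze*: "We hypothesize that there is a 15% absolute differences in efficacy between the groups, measured in clinical efficacy", then "Assuming an efficacy of 90 and 75% for 5 days and 3 days therapy, respectively", "using a double-sided test with" a 0.05 threshold and "a statistical power of 0.8". This gives 113 per group for the need-to-treat (NTT) set, 161 for per-protocol (PP) and 230 for intention-to-treat (ITT). No day is attached to the two rates.
- *Questionnaires*: inclusion is day 0, and "All participants will be given a diary-questionnaire for day 0 to day 7".
- *Microbiological diagnostics* puts the first control urine at day 8–10. *Outcomes*, in the Discussion, places a follow-up urine at day 4.
- *Scientific and societal perspective* foresees keeping the 3-day regimen if it proves non-inferior.

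**The concern.** The randomised contrast is active drug against placebo on days 4 and 5. A cure proportion read on day four is taken when that contrast has only begun or, at the latest, is just finishing. The assumed rates describe what each whole course achieves, so they need not apply on that day. If part of the benefit of the longer course appears after day four, this comparison cannot count it.

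The dilution runs one way, towards no difference. That matters because the Discussion gives clinical effect the most weight and treats similar results as grounds for keeping the shorter course. A weak day-four contrast could then be read as evidence of equivalence when it reflects the timing of the measurement.

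**Working it through.** **1. Reproduce the stated sample size.** Inputs from *Power analyze*: p1 = 0.90, p2 = 0.75, difference d = 0.15, two-sided 0.05, power 0.80. Equal allocation is taken from the equal group sizes. The mean rate is 0.825.

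Pooled formula: n = [z(0.975)·√(2·0.825·0.175) + z(0.80)·√(0.90·0.10 + 0.75·0.25)]² / 0.15² = [1.0532 + 0.4434]² / 0.0225 = 99.5, that is 100 per arm.

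With continuity correction: n′ = (n/4)·[1 + √(1 + 4/(n·d))]² = (99.54/4)·[1 + √(1 + 4/14.93)]² = 112.5, that is **113**, as stated.

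Losses: 113/0.7 = 161.4 (stated 161) and 161/0.7 = 230.0 (stated 230). The arithmetic is sound. What is open is the day to which the 15 points belong.

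**2. How far the arms differ at day four.** Two numberings fit the text.

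| Numbering | Diary day 4 is | Days of differing tablets by then | Last day of 5-day course |
|---|---|---|---|
| Placebo days use diary numbering | treatment day 4 | at most 1 | diary day 5 |
| First dose on day 0 counts as treatment day 1 | treatment day 5 | up to 2 | diary day 4 |

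Cure is read before, or just as, the 5-day course ends. Diary day 7 falls after both courses under either numbering.

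**3. What 90% v 75% at day four would require.** Let c be the common cure rate when the arms diverge (not given, so assumed). Among women uncured at that point, the share cured by the day-four reading must be (0.75 − c)/(1 − c) in the 3-day arm and (0.90 − c)/(1 − c) in the 5-day arm:

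| c | 3-day arm | 5-day arm |
|---|---|---|
| 50% | 50% | 80% |
| 60% | 37.5% | 75% |
| 75% | 0% | 60% |

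These are scenarios, not figures from the plan. In each, one day of tablets (at most two) must produce the whole gap.

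**4. Power if the day-four gap is smaller.** The test is Fisher's exact test, as named under *Data processing and statistical analysis*, two-sided 0.05, by full enumeration. The 3-day arm is held at 75% and the gap is assumed.

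| Gap at day four | 113 (NTT) | 161 (PP) | 230 (ITT) |
|---|---|---|---|
| 15 points | 82% | 93% | 99% |
| 10 points | 41% | 56% | 73% |
| 7.5 points | 23% | 33% | 46% |
| 5 points | 11% | 16% | 22% |

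The continuity-corrected formula of step 1 gives the number per arm for 80% power: 270 for 10 points, 493 for 7.5 and 1,134 for 5.

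**The case against.** The strongest reply is that day-four cure is only part of the primary assessment. The clinical co-primary also asks which arm is cured faster, and the daily diary to day 7 can register cures after the arms diverge. The bacteriological co-primary is read at day 8–10 according to *Microbiological diagnostics*, after both courses, and the authors expect a larger difference there. This stands: the trial is not blind to later effects, although time to cure also includes the days on which treatment is identical.

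A reader might infer that the day-four endpoint cannot show a 15-point effect, or that a null result would say nothing about 3 v 5 days. The documents support neither. They give no cure rate at day three or day four, so a 15-point gap is doubtful rather than impossible, and the other co-primary information remains.

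A reader might also take one day of differing tablets as settled, or treat the 60% in the last row of step 3 as the plan's own figure. The first depends on a day numbering the article leaves open. The second holds only if 75% are cured when the arms diverge and no further woman in the 3-day arm is cured by the reading.

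Finally, power at 113 per arm alone would overstate the loss, because the PP and ITT sets are larger. For a 10-point gap power reaches 73% in ITT. For a 5-point gap it is low in every set.

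**Conclusion.** The point holds in this form: the only proportion in the clinical co-primary is timed to the start of the treatment contrast, and the effect assumed for complete courses is not tied to that time. The comparison is probably diluted towards no difference and is unlikely to reach the stated 80% power. If half the assumed effect (7.5 points) has appeared by day four, power is below 50% in all three analysis sets.

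The size of the loss rests on two assumptions that the documents do not settle: the visible gap at day four and a 75% cure rate in the 3-day arm on that day. The timing mismatch does not depend on either, and it remains under both day numberings. A day-four null would be weak evidence on 3 v 5 days and should not be used to support keeping the 3-day course.

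**What to change.** - *Primary endpoint*: read the clinical co-primary proportion (symptom score below 2) on diary day 7. Make day-four cure secondary. Time to cure may stay as a supporting measure.
- *Power analyze*: name the time point to which 90% and 75% apply and justify the rates there, or restate the power. Declaring that they hold at day 7 is not enough, because nothing in the article supports them at that day either. If they can be supported, 113/161/230 stand. If day four is kept, justify a day-four effect and resize for it.
- *Intervention* and *Questionnaires*: define how treatment days map to diary days, given that inclusion is day 0.
- *Microbiological diagnostics* and *Outcomes*: reconcile the first control urine (day 8–10 against day 4).

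Cost: an amendment before unblinding. No new data are needed, because the diary already covers day 7. The downside is that the endpoint departs from the authors' choice and the assumed rates need support at the new time point.
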